## 1 Summary

Coronary artery disease (CAD) is a major public health issue accounting for 20% of all deaths in Germany and affecting 13.2 million persons and causing more than 500,000 deaths in the United States each year. Commonly coronary artery stenoses are treated using stent placement. The follow-up of these stents for detection of in-stent restenoses is currently based on (invasive) conventional coronary angiography as the definite reference standard, which is performed for diagnostic purposes in more than three out of four cases after stent treatment. Over the last years two noninvasive diagnostic tests for CAD diagnosis have been developed - multislice computed tomography (MSCT) and magnetic resonance imaging (MRI). Due to metal-related artifacts MRI is not suited for detection of coronary artery in-stent restenoses. Despite that MSCT is less limited by such artifacts diagnostic accuracy of MSCT for detection of in-stent restenoses has varied greatly among studies using 16- and 64-slice configuration. The primary aim of this study is to demonstrate a per-patient diagnostic accuracy of combined 320-slice CT for coronary angiography (CTA) and myocardial perfusion (CTP) significantly greater than 75% at an expected per-patient diagnostic accuracy of 87%. For this purpose at a power of 80% and an alpha level of 0.05 altogether 90 patients will have to be recruited.

## 2 General Information

### Title

Coronary Artery Stent Evaluation With 320-slice Computed Tomography (“CArS 320 Study”)

### 3 Background

#### Coronary Artery Stents

Coronary artery disease (CAD) is a major public health issue, for instance in the United States CAD affects 13.2 million persons and is responsible for more than 500,000 deaths each year (American Heart Association. Heart Disease and Stroke Statistics – Update. 2004), while in Germany 20% of all deaths are due to CAD (Gesundheitsbericht). CAD diminishes local, regional, or global blood supply to the heart and is most commonly caused by coronary atherosclerosis. CAD may manifest as angina pectoris, myocardial infarction, sudden cardiac death, or as severe cardiac insufficiency in ischemic cardiomyopathy. Commonly coronary artery stenoses are treated using stent placement. The follow-up of these stents for detection of in-stent restenoses is currently based on (invasive) conventional coronary angiography as the definite reference standard, which is performed for diagnostic purposes in more than three out of four cases after stent treatment. MSCT is a fast and reliable diagnostic tool to noninvasively assess the coronary arteries for stenoses (Hoffmann et al. JAMA 2005, Dewey et al. 2006 Annals of Internal Medicine 2006). Besides detection of stenoses in the native coronary arteries, assessment of coronary artery in-stent restenosis is of increasing clinical importance as the number of catheter-based coronary interventions is on the rise (currently more than 200,000 in Germany per year). Thus, a reliable noninvasive alternative would be an important clinical improvement.

#### Economic Considerations

From what has been outlined above it is obvious that diagnosis and therapy of CAD are frequent events and thus account for a considerable part of health care reimbursement. The average expenditure for each patient with CAD is approximately € 64,000 (1). With a decreasing mortality and an increasing number of patients since the 1970s, the direct annual expenditure for outpatient and inpatient treatment in Germany was 2.73 billion (1995) and 3.36 billion € (1996) (1). In the US the overall cost of an AMI including acute catheter intervention, cardiac rehabilitation, and subsequent loss of working hours is \$73.000 on average (2). The US spent an estimated \$111.8 billion on CAD in 2002 (3). Currently, conventional coronary angiography is performed 874,648-times per year at costs of at least 630 € for each examination. With MSCT and costs of approximately 175 € there is the potential to significantly reduce health care costs provided that clinical efficacy in clinical management can be proven (4). Thus, this trial will influence both clinical and economical approaches to diagnosis and management of coronary

artery disease in Germany and other countries.

## Conventional Coronary Angiography

Conventional coronary angiography is the reference standard for definitive diagnosis of coronary artery in-stent restenoses (Guideline of the German Cardiac Society. Diagnose und Behandlung der chronischen koronaren Herzerkrankung). According to the latest report of the German Cardiac Society, over 700,000 conventional coronary angiographies were performed in 2003 (5). Approximately three out of four conventional coronary angiographies performed for follow-up of patients with coronary stents are for diagnostic purposes only since relevant lesion can be excluded in these patients. To replace these diagnostic examinations with noninvasive modalities would be worthwhile. Moreover, conventional coronary angiography carries a risk of complications that is not negligible (6). This problem may be overcome by the use of noninvasive coronary angiography.

## Noninvasive MSCT Coronary Angiography (CTA)

With the recent multislice CT (MSCT) scanners using submillimeter detector collimation and thus isotropic voxel sizes of down to  $0.5 \times 0.35 \times 0.35$  mm, reliable detection of coronary artery in-stent restenoses is feasible but has shown rather variable results in several studies comparing MSCT to conventional coronary angiography (**Table 1**). It is noteworthy that in the studies including all patients with coronary stents regardless of internal stent diameter (7-9), a considerable proportion of stents had to be excluded from analysis due to poor image quality. Adequate evaluation with an accuracy suitable for clinical use was possible only for stents with an internal diameter of at least 3.5 mm (7). An only moderate diagnostic accuracy was achieved in those segments that could be evaluated (Table). In contrast to these results, two studies investigating only patients with stents in the left main branch found a fairly high sensitivity of over 90% (10, 11). Two further recent studies investigating stents in all coronary arteries as well as bypass grafts in a total of 64 (12) and 143 patients (13) suggest that adequate assessment of the stent lumen is possible only in about 50% of all stents with an internal diameter of up to 3.0 mm. Therefore, sensitivities and specificities are very poor when all stents are included in the analysis (**Table 1**). Altogether, these results show that current MSCT scanners still have marked limitations in the detection of coronary artery in-stent restenoses. These limitations might be overcome if, in addition to improving spatial and temporal resolution, information on blood flow can be obtained. Myocardial blood flow cannot be assessed with currently available CT scanners because they do not yield functional information. Moreover, small stents cannot be reliably assessed due to their small diameter and beam hardening artefacts. The next generation of 320-

slice scanners currently being developed (14) provide functional information (4D analysis) that allows evaluation of blood flow and therefore might improve the evaluation of coronary stents.

**Table 1 Results of a Systematic Review for the Comparison of MSCT and Conventional Coronary Angiography for Detection of Coronary Artery In-Stent Restenoses\***

| Author                        | Total No. of stents | Stents excluded† | Prevalence (%) | Sensitivity (%) | Specificity (%) |
|-------------------------------|---------------------|------------------|----------------|-----------------|-----------------|
| Schuijf (7)                   | 65                  | 15 (23%)         | 18             | 78              | 100             |
| Kitagawa (8) §     | 35                  | 19 (54%)         | 31             | 100             | 100             |
| Cademartiri (9) ¶  | 76                  | 2 (3%)           | 8              | 83              | 99              |
| Gaspar (15) ¶      | 111                 | 0                | 20             | 64              | 88              |
| Gilard (10) §      | 29                  | 2 (7%)           | 15             | 100             | 100             |
| van Mieghem (11) § | 74                  | 0                | 15             | 91              | 87              |
| Gilard (13) ¶      | 232                 | 0                | 9              | 50              | 53              |
| Rixe (12) ¶        | 102                 | 0                | 12             | 50              | 57              |

\* The table (modified from Dewey and Hamm, Röfo 2007) lists only those studies in which the sensitivity and specificity for the detection of in-stent restenoses are given in comparison to conventional coronary angiography and which investigated CT scanners with at least 12 simultaneous detector rows.

† Number of stents excluded from the calculation of accuracy due to poor image quality. This procedure is in contrast to the recommendations for the conduct and publication of diagnostic studies of the STARD initiative (16).

§ Only a subgroup of the study patients underwent conventional coronary angiography.

§ The study included only stents of the left main branch. This reflects the great differences that exist between published studies, which is why no accumulation of the accuracy data for the detection of in-stent restenoses over all studies was done.

¶ These studies also included (a small number of) stents in venous coronary bypass grafts.

## Implications for the Design of the Present Study

As shown above the diagnostic performance of MSCT for detection of in-stent restenoses is rather variable and in some studies a remarkable number of patients/stents was excluded from analysis because of poor image quality. This is why the diagnostic performance of MSCT is overestimated. On the other hand, only with 320-slice information in regards to blood flow based on the 4D nature of the scanner are available as myocardial perfusion information (with and without adenosine) and are likely to further improve diagnostic performance. Thus, we expect a diagnostic per-patient accuracy of 87% in our study. Most importantly, a fair analysis of the

---

clinically relevant performance of MSCT needs to be conducted in an intention-to-diagnose fashion (including all stents regardless of size, location, and image quality). This approach will be used in the present study.

In conclusion, the potential clinical benefit of 320-slice CT for detection of in-stent restenoses should be analyzed using a combined assessment of myocardial perfusion and angiography, in those patients where coronary CT angiography is not evaluable, in comparative study with conventional coronary angiography as the gold standard and an intention-to-diagnose design to represent the clinical value of this new test most appropriately.

## 4 Trial Objectives

### Primary Objective

The primary objective of this study is to analyze the diagnostic accuracy of MSCT using 320 simultaneous detector rows for coronary CT angiography (CTA) and myocardial perfusion (CTP) for the detection of coronary artery in-stent restenoses in comparison to conventional coronary angiography.

The hypothesis will be to demonstrate a per-patient diagnostic accuracy of 320-slice CTA with CTP significantly greater than 75% at an expected per-patient diagnostic accuracy of 87%. For this purpose at a power of 80% and an alpha level of 0.05 altogether 90 patients will have to be recruited.

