### Withdrawal

Reasons for early withdrawal from a study may include but are not limited to:

1. Patient withdraws consent.
2. Any medical condition or situation that in the opinion of the investigator exposes the patient to significant risk by continuing the study.
3. Any serious adverse event, clinically significant event, or severe laboratory abnormality that may significantly increase the patient's risk in continuing in the study.

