### **Other Information**

If the patient has had an interim change in cardiac clinical status (e.g. worsening of symptoms requiring immediate catheterization without CT), then the patient will be excluded from the analysis.

The MSCT raw data and reconstructed data will be saved at each site for at least 30 years after completion of the study.

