## 11 Statistics

Since the benefit of the non-invasive technology, if it exists, should not be withheld from potential beneficiaries for unreasonably long time, and on the other hand the technology might infiltrate medical practice without scientific evidence of benefit, if trial time is too long, it was agreed to aim at a study size allowing for getting results within a 2 years period. Power should be at least 80% with a type I error of  $\alpha = 0.05$  (two-sided).

The primary objective of this study is to analyze the diagnostic accuracy of MSCT using 320 simultaneous detector rows for detection of coronary artery in-stent restenoses in comparison to conventional coronary angiography.

We expect a per-patient diagnostic accuracy of combined CTA and CTP of 87% in comparison to conventional coronary angiography. 90 patients are needed to detect these differences with a power of 80% and an alpha level of 0.05.

The statistical design and all statistical analyses will comply with the International Conference on Harmonization (ICH) Guidance for Industry: E9 Statistical Principles for Clinical Trials.

The assumptions for diagnostic accuracy of MSCT are based on the previous studies published (**Table 1**) and the expected improvement using 320-slice CT.

Secondary endpoints will be evaluated using t-tests, Mann-Whitney-U-tests,  $\chi^2$ -tests, or survival analysis according to scaling. Subgroups (gender, age groups, symptoms) will be analyzed exploratively.

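### The 90 patients to be recruited are also the 90 needed in the analysis, so the stated power of at least 80% makes no allowance for the withdrawals and exclusions that the protocol foresees

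*Protocol*

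**What the plan says.** The number 90 does three jobs in the protocol.

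- **Number needed.** Section 11 (Statistics) says "90 patients are needed to detect these differences with a power of 80% and an alpha level of 0.05". The same section sets the requirement: "Power should be at least 80% with a type I error of" 0.05, two-sided.
- **Number recruited.** Section 1 (Summary) and Section 4 (Primary Objective) both give it as the recruitment number: "For this purpose at a power of 80% and an alpha level of 0.05 altogether 90 patients will have to be recruited". Section 12 (Methods Against Bias) ties recruitment to the sample size calculation.
- **Number analysed.** Section 5 (Number of Participants and Duration) says that 90 patients will be included and analysed by intention to treat.

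Two other places provide for patients to drop out between recruitment and analysis. Section 5 (Withdrawal) has an open list, introduced by "Reasons for early withdrawal from a study may include but are not limited to", that covers withdrawn consent, medical risk, serious adverse events and laboratory abnormalities. Section 7 (Other Information) deals with patients whose cardiac status changes in the interim, for example those who need immediate catheterisation without CT: "then the patient will be excluded from the analysis".

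No loss rate, inflation of the sample size or replacement of lost patients is stated.

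**The concern.** A sample size formula gives the number of patients who contribute to the test. Here each must have both a CT result and a conventional angiography result. If the recruitment number equals that figure, every loss comes straight out of the power, and the protocol itself names routes by which patients are lost. Inclusion to CT may take up to 14 days, and CT to angiography up to 14 more (Section 13), so some interim changes are plausible.

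At stake is whether the stated power is true of the trial as it will be run. The passages also disagree on the analysed population: Section 5 has all 90 analysed, while Section 7 removes some of them.

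**Working it through.** **Inputs.** Null accuracy p0 = 0.75 and expected accuracy p1 = 0.87 (Primary Objective and Section 11); alpha 0.05 two-sided and power of at least 80% (Section 11).

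**Reproducing the 90.** The one-sample formula for a proportion, with null and alternative variances, is

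n = [(z₀.₉₇₅·√(p0(1−p0)) + z₀.₈₀·√(p1(1−p1))) / (p1−p0)]²

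= [(1.960·√0.1875 + 0.8416·√0.1131) / 0.12]²

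= [(0.8487 + 0.2830) / 0.12]² = 88.95, so 89.

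The exact binomial test (upper tail at most 0.025) also first reaches 80% power at 89. With 90 it declares success at 76 or more correct, with upper-tail error 0.0218 and power 81.3%. The stated 90 is therefore confirmed, and the margin over the minimum is 90 − 89 = 1 patient.

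**Power when fewer are analysed.** The normal approximation is

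power = Φ[(0.12·√n − 1.960·√0.1875) / √0.1131].

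For example, n = 81 gives Φ[(1.0800 − 0.8487) / 0.3363] = Φ(0.688) = 75.4%. The last two columns are exact binomial power at p1 = 0.87, first for the exact test and then for an uncorrected score test (reject if z ≥ 1.96).

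| Analysed | Normal approximation | Exact test | Score test |
|---|---|---|---|
| 90 | 80.6% | 81.3% | 81.3% |
| 89 | 80.0% | 82.4% | 82.4% |
| 88 | 79.5% | 75.0% | 83.5% |
| 87 | 78.9% | 76.4% | 76.4% |
| 86 | 78.4% | 77.7% | 77.7% |
| 85 | 77.8% | 79.0% | 79.0% |
| 84 | 77.2% | 70.6% | 80.2% |
| 83 | 76.7% | 72.1% | 81.5% |
| 81 | 75.4% | 75.0% | 75.0% |

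By the first two methods, every number checked from 88 down to 70 is below 80%. The score test is saw-toothed and still exceeds 80% at 88, 84 and 83. Its actual upper-tail error at those sizes is 0.0251 to 0.0287, slightly above 0.025.

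**Assumed losses (not in the protocol).** A 5% loss leaves 90 × 0.95 = 85.5, so 85 or 86 analysed: 77.8 to 78.4% by the approximation, 77.7 to 79.0% exact. A 10% loss leaves 90 × 0.90 = 81: 75.4% and 75.0%. At 85, 86 and 81 all three columns are below 80%.

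**The case against.** The strongest reply is that nothing has been miscalculated and that losses should be few. Patients are already scheduled for clinically indicated angiography, all of them undergo it whatever the CT shows (Section 12), and the imaging period is expected to last under a week (Section 5). Poor image quality is no reason for removal. At an assumed 5% loss the shortfall is only 1 to 2 points. All of this stands, and it limits the size of the point. It does not remove it, because the protocol sets at least 80% as a requirement, names routes of loss and allows nothing for them.

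A reader might infer more than the documents support, in four ways.

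- **That 90 is an arithmetic error.** It is not; two methods reproduce it.
- **That losing two patients necessarily takes power below 80%.** This depends on the test, and the protocol names none for the primary hypothesis. At 88 analysed, power is 79.5%, 75.0% or 83.5% by the three methods above.
- **That lost patients count as wrong diagnoses under intention to diagnose,** which would cut power much further. The protocol uses that principle to keep patients and stents with poor image quality (Sections 3 and 5). No section scores a patient without CT or angiography as incorrect, and Section 7 excludes interim-change patients.
- **That success can be fixed as at least 76 of 90 correct.** That cutoff applies only if all 90 are analysed; for the exact test it becomes 72 of 85 or 69 of 81.

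A one-sided alpha of 0.05 would leave ample room (88.1% exact power at 90), but Section 11 says two-sided.

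The analysis plan, which is not shown, may define the analysis sets. The recruitment number, the power claim and the exclusion rule are nevertheless all fixed in the protocol, and it is there that they disagree.

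**Conclusion.** The point holds as a missing allowance for losses. The calculation of 90 is sound, but a power of at least 80% for 90 recruited patients is not secured: the margin is about one patient by the normal approximation and the exact binomial test. With assumed losses of 5% and 10%, power is about 78 to 79% and about 75%. These figures rest on 87% true accuracy, a 75% null value, two-sided 0.05, and lost patients being left out of the analysis. The loss rates are illustrations. The trial is not invalidated, but its stated power should be true of the patients it will actually analyse, and Sections 5 and 7 should agree on who they are.

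**What to change.** In Section 1, Section 4 (Primary Objective), Section 5 (Number of Participants and Duration) and Section 11, state that 80% power refers to 90 patients with both CT and conventional angiography in the analysis.

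If 90 remains the recruitment number:

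- give a loss assumption and restate the power under it, about 78% at 5% loss or about 75% at 10%, naming the method used, because exact power does not change smoothly with n;
- amend the requirement of at least 80% in Section 11 to match, since a lower stated power would otherwise contradict it;
- reconcile the Section 5 statement that all 90 will be analysed with the exclusion in Section 7 (Other Information).

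No fixed success count should be written in, because it changes with the number analysed.

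The cost is a slightly less favourable stated power and a few reworded sentences; no extra patients are needed on this route. If the sponsor would rather secure 90 analysed patients, recruitment becomes 90/0.95 = 94.7, so 95, at 5% loss, or 90/0.90 = 100 at 10%.

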### Secondary Objectives

1. To analyze per-patient sensitivity, specificity, and receiver-operating characteristic curves.
2. To analyze per-stent accuracy, sensitivity and specificity, and receiver-operating characteristic curves. For this analysis a statistical adjustment for clustering of stents within patients will be conducted using nonparametric analysis of variance.
3. To analyze interobserver variability in detection of coronary artery in-stent restenoses using MSCT.
4. To compare diagnostic accuracy for stents in different locations (coronary vessels), of different size and length, and for stents made of different materials.
5. To analyze the influence of different scan (heart rate, heart rate variability) and patient characteristics (gender, age, diabetes, body mass index) on image quality and diagnostic accuracy of MSCT.
6. To compare procedural complications of MSCT and conventional coronary angiography. These complications will include.
  - death,
  - stroke, and
  - myocardial infarction and
  - moderate to severe groin hematoma, groin pain, infections, allergies, thromboses, and arteriovenous fistula or other complications (if prolonging the in-hospital stay significantly [by at least 24 hours]).

- 
7. To analyze the cost-effectiveness using the primary and secondary efficacy data, the QALY data, and cost data derived from the trial.
  8. To analyze patient preference and satisfaction with and comfort during the imaging tests as recently described (Schönenberger et al. PLoS ONE 2007).
  9. To compare the amount of contrast agent and radiation exposure and the room time required (excluding time for interventions) of both tests.
  10. In addition, noncoronary causes of symptoms (e.g. pulmonary embolism, aortic dissection, pericarditis, pleural effusion, pneumonia, or hiatal hernia) will be recorded to analyze whether the cross-sectional imaging capabilities of MSCT might lead to a higher detection rate of those important incidental findings.
  11. To analyze which image quality in MSCT coronary angiography is required to directly reliably triage patients with suspected coronary artery in-stent restenoses.
  12. To analyze the correlation and agreement between MSCT coronary angiography and conventional coronary angiography (using quantitative analysis) for estimation of the percent diameter stenosis.

